## Sample size

The number of participants to be included in the study was calculated on the basis of the change in body weight. We used the difference in weight change observed between the control and intervention group (1.04 Kg) in Ruiz et al. [20] as the expected effect size. A total of 52 women (26 per group) will be needed to detect a mean group difference of 1.04 and a standard deviation of 1.15 Kg in weight change with a power of 90 % and α of 0.05. However, we will exceed this sample size to allow for withdrawals. Assuming a maximum lost-to-follow up of 15 % [20], we will recruit a total of 30 participants per group (*n* = 60).

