**Fig. 1 Fig1:**
[figure not shown]
Organizational and participants flow

The inclusion and exclusion criteria are described in Table 1. Participants will have to provide a written informed consent before taking part in the study, which will be conducted in accordance with the CONSORT (Consolidated Standards of Reporting Trials) statement [50]. Moreover, women will have to answer “No” to all questions from the PARmed-X for pregnancy health checklist (Physical Activity Readiness Medical Examination) by the Canadian Society for Exercise Physiology [51].

**Table 1 Tab1:** Inclusion and exclusion criteria in the GESTAFIT project

Inclusion criteria	
- Overweight or grade I obese pregnant woman aged 25–40 years old with a normal pregnancy course.	
- Answer “no” to all questions on the PARmed-X for pregnancy*.	
- To be able to walk without assistance.	
- To be able to read and write enough.	
- Informed consent: To be capable and willing to provide consent.	
*In addition, specific inclusion criteria for data analysis are: gestational age at delivery of 37–42 weeks with single foetus, spontaneous vaginal delivery or instrumental vaginal and caesarean without maternofoetal pathology (or other indication that does not involve maternofoetal risk, such as disproportion, failed induction, no foetal progression or non-cephalic presentation), newborn with appropriate weight, Apgar score > 7 in the 1st and 5th minute of life, cord blood pH (normal > 7.20) and normal monitoring results.	
Exclusion criteria	
- Acute or terminal illness.	
- Malnutrition.	
- Inability to conduct tests for assessing physical fitness or exercise during pregnancy.	
- Underweight, normal-weight or grade II-III obesity.	
- Pregnancy risk factors (such as hypertension, type 2 diabetes, etc.).	
- Multiple pregnancies.	
- Chromosopathy or foetal malformations.	
- Uterine growth restriction.	
- Foetal death.	
- Upper or lower extremity fracture in the past 3 months.	
- Presence of neuromuscular disease or drugs affecting neuromuscular function	
- Be registered in other exercise program	
- Perform more than 300 min of at least moderate physical activity per week	
- Unwillingness to either complete the study requirements or to be randomised into control or intervention group.	

PARmed-X for pregnancy: Physical Activity Readiness Medical Examination

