## Statistical analysis

Since this study aims at determining potential biological effects of exercise, the statistical analysis will be performed on a per-protocol basis, thus, including in the analyses only participants who attended at least 80 % the exercise session and completed both baseline and follow-up evaluations. The treatment effects will be reported as between-group changes on the primary and secondary outcomes and will be assessed with generalized linear models after adjusting for baseline values. All the analyses will be repeated additionally adjusting for age and any other confounder potentially not well balanced at baseline, and the results from both models will be reported. The effect size (95 % confidence interval) and statistical significance will be reported for each study outcome. The statistical significance will be set at α = 0.05. Sensitivity analyses will be conducted using intention-to-treat analyses and baseline observation carried forward imputation.

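### The 90% power is calculated for 52 analysed women after withdrawals only, but the per-protocol attendance rule and the birth-outcome criteria remove further women and neither is allowed for

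*Protocol article*

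**What the plan says.** All references are to the protocol article.

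- **Sample size.** The calculation rests on change in body weight, with a difference of 1.04 kg and "a standard deviation of 1.15 Kg in weight change". It concludes: "A total of 52 women (26 per group) will be needed", "with a power of 90 % and α of 0.05". The number is then raised to allow for withdrawals, with a maximum loss to follow-up of 15%: "we will recruit a total of 30 participants per group".
- **Statistical analysis.** The main analysis is per-protocol. It keeps only women who attended at least 80% of the exercise sessions "and completed both baseline and follow-up evaluations". Intention-to-treat with baseline observation carried forward is a sensitivity analysis.
- **Table 1.** A note under the inclusion criteria adds a further filter: "specific inclusion criteria for data analysis are: gestational age at delivery of" 37–42 weeks, followed by conditions on type and indication of delivery, newborn weight, Apgar score, cord blood pH and monitoring.
- **Primary outcome.** Weight gain, the outcome used for the sample size, is measured from baseline to week 34, before delivery.

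**The concern.** A power statement should describe the set of women on whom the main test is run. Here the number analysed is fixed at 52 and the number recruited at 60, and the only thing between them is loss to follow-up. The article's own rules remove women for two other reasons: low attendance in the exercise group and, on the natural reading of Table 1, an unfavourable birth outcome in either group. A woman can complete every evaluation and still be dropped on either ground, so she is not a withdrawal.

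Both the sample size and the analysis-set rules are fixed in this document, so the mismatch is not a detail left to a later analysis plan. If it stands, a null per-protocol result will be read against a 90% claim that does not belong to that analysis.

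**Working it through.** **Inputs.** Difference 1.04 kg, SD 1.15 kg, α 0.05, power 90%, 15% loss, 30 per group (all from Sample size). Sidedness is not stated; two-sided is used because it reproduces the stated number, whereas one-sided gives 21 per group.

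**Step 1: the plan's own figure.** Standardised effect d = 1.04/1.15 = 0.904.

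n per group = 2 × (1.960 + 1.282)² / d² = 25.7, so 26 per group and 52 in total. This reproduces the article. Power at 26 per group is 90.3% by the normal formula and 89.2% by the t-test (the t-test would need 26.7, so 27 per group).

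**Step 2: the allowance for withdrawals.**

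- Multiplying: 26 × 1.15 = 29.9, so 30 per group. This matches the article.
- Dividing by the share retained: 26 / 0.85 = 30.6, so 31 per group, 62 in total, leaving 62 × 0.85 = 52.7.
- With 60 recruited: 60 × 0.85 = 51 (25.5 per group). Power is 89.8% (normal) or 88.6% (t-test).

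This step alone costs about half a percentage point. It does mean that no margin is left at the stated maximum loss.

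**Step 3: the exclusions not allowed for.** Let a be the share of exercise-group completers who reach the attendance threshold, and b the share in both groups who meet the birth criteria. The attendance rule is applied to the exercise group only, since controls have no exercise sessions to attend. Then

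n₁ = 25.5 × a × b (exercise), n₂ = 25.5 × b (control),

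and power is that of a two-sided, two-sample t-test with n₁ + n₂ − 2 degrees of freedom and noncentrality d / √(1/n₁ + 1/n₂). **The document gives no value for a or b; every row below except the first rests on assumed rates.**

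| Lost on attendance (exercise group) | Lost on birth criteria (both groups) | n₁ / n₂ | t-test power |
|---|---|---|---|
| 0% | 0% | 25.5 / 25.5 | 88.6% |
| 10% | 0% | 22.9 / 25.5 | 86.8% |
| 20% | 0% | 20.4 / 25.5 | 84.5% |
| 10% | 10% | 20.7 / 22.9 | 83.0% |
| 20% | 20% | 16.3 / 20.4 | 75.4% |
| 30% | 30% | 12.5 / 17.8 | 65.8% |

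In these rows the normal approximation is about 1 to 3 points higher.

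**Step 4: the room that exists.** To keep 26 per group from 30, at most 4 women per group (4/30 = 13.3%) may be lost for all reasons together: withdrawal, attendance and birth outcome.

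**The case against.** Several points on the other side stand.

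- **The 51 versus 52 gap is trivial.** Power changes by about half a point. The 15% is also a maximum: if loss is 13.3% or less, 60 recruits still give 52 completers. The inflation slip is a remark and not the main point.
- **The size of the shortfall is unknown.** A reader might take the lower rows of the table, or something lower still, as the trial's actual power. The document does not support that. To reach about 55%, 40% of exercise completers would have to miss the threshold and 40% of both groups would have to fail the birth criteria, and nothing in the text points to such rates. Table 1 keeps instrumental births and caesareans for several listed indications, and enrolment excludes risk pregnancies; both argue against the heaviest scenarios without fixing a rate.
- **The losses may overlap.** The table multiplies them. If women who drop out would also have been low attenders, power is somewhat higher than shown.
- **The reach of the birth criteria is unclear.** Table 1 does not say which outcomes they govern, and Statistical analysis does not mention them. Applying them to a weight change measured at week 34 is a fair reading but not a certain one. If they do not apply, only the attendance rows are relevant.
- **Other influences are not counted.** Baseline adjustment could raise power, and unequal groups under simple randomization could lower it. Neither can be quantified from the document.

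A reader might also infer that the SD of 1.15 kg is wrong because no source is attached to it. That does not follow: the study cited for the difference and the loss rate may supply it, and the document offers no competing value.

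None of this removes the mismatch. The allowance is for withdrawals, and the main analysis excludes women for at least one further reason.

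**Conclusion.** The concern holds as an omission with a known direction and an unknown size. The 52 reproduces, and at the stated maximum loss the 60 recruits leave 51 completers with about 89–90% power. From there, any exclusion for attendance or birth outcome lowers the power of the main analysis further, so 90% is not a valid statement about that analysis under the article's own assumptions.

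The illustrative figures (about 85%, 83%, 75% and 66%) depend on the assumed rates, on the stated difference and SD, and on losses that do not overlap. Mild exclusion keeps power above 80%. Confidence is high for the missing allowance and low for any particular power value.

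**What to change.** Keep 60 women and amend the text as follows.

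1. In Sample size, state that 15% loss leaves 51 completers, with about 89% power at 1.04/1.15 before further exclusions.
2. Add the power for the per-protocol set, with the expected attendance and birth-criteria rates written down; a short table over a few rates is enough.
3. In Table 1 or Statistical analysis, state whether the birth criteria apply to the week-34 weight-change outcome.

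The 51 women and the 89% should not be attributed to the intention-to-treat analysis. As planned, with baseline carried forward, that analysis keeps all 60. Women without follow-up enter it with a weight change of zero, and low attenders stay in, so the 1.04 kg difference may be diluted. Its power is a separate figure and should be given separately if it is quoted.

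The cost is a few sentences and a less favourable power figure. No extra participants are needed.

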## Randomization and blinding

After all the baseline evaluations, participants will be randomized to either the exercise intervention or the control group. A computer generated simple randomization sequence will be created before participants will be enrolled, to allocate participants to either group (1:1). The randomization sequence will be prepared by a member of the research team with no clinical involvement in the trial. The allocation will be concealed in a password protected computer file. Whereas the participants will be aware of their group allocation, outcome assessors and data analysts will be blinded to the allocation.

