## Exercise intervention

Most of exercise programs developed for pregnant women until now [20, 27, 52] have been designed in compliance with the recommendations of the American College of Obstetrics and Gynaecology (ACOG) in 2002 [53], or the Canadian Society for Exercise Physiology, among others [54]. However, in 2011, Zavorsky & Longo [55] launched a more actual, specific, and evidence-based guideline for exercise programs during pregnancy. Consequently, the exercise program that will be conducted in the present project has been developed accordingly to this guideline [55]. Nonetheless, we have also followed similar studies [56, 57] where aerobic and resistance training, as well as strengthening of the pelvic floor muscles [58], have been developed successfully and in line with these recommendations [57].

The exercise intervention (*n* = 30) will be performed in three groups of 10 participants and will meet the training standards of the American College of Sports Medicine [59] for adults. The groups will train 3 days/week (55–60 minutes per session) from the 17th week of gestation until delivery. The exercise sessions will be designed, carefully supervised, guided and instructed by qualified exercise professionals with experience in working with pregnant women.

The exercise program planning is shown in Table 3. The exercise intervention group will have different phases: a) *Information phase*: which will involve the understanding of the intervention plan for them, the goals we want to work with them, and how we will perform it (one training session); b) *Movement Learning phase*: theoretical and practical sessions with the explanation of movements and explanation of basic movement patterns (two training sessions); and c) *Physical Fitness Training phase*: with training sessions aimed at improving fitness and weight management (from the 18th until the 34th gestational week), and training sessions focused on a correct pelvic mobilization for the delivery (after the 34th gestational week until delivery) in order to try to reduce caesarean section rate, delivery time and number of pushes [23, 60].

**Table 3 Tab3:** Supervised exercise intervention program

SESION STRUCTURE	CONTENT										
WARM-UP 10 min	Joint mobility and different walk modalities										
CONDITIONING 40 min	Training week	1	2–4	5–6	7–8	9–10	11–12	13–14	15–16	17–18	>19
	Gestational week	17	18–20	21–22	23–24	25–26	27–28	29–30	31–32	33–34	>34

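### Simple randomisation of 60 women will rarely give the stated 30 per group and three classes of 10, and it does nothing to control BMI class

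*Protocol article*

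**What the plan says.** Randomization and blinding: "A computer generated simple randomization sequence will be created before participants will be enrolled, to allocate participants to either group (1:1"). The section mentions no blocking, stratification or minimisation. A team member without a clinical role prepares the list, women are randomised after all baseline evaluations, and participants know their group.

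Other sections give the arm sizes as exact numbers. Sample size: "we will recruit a total of 30 participants per group". Exercise intervention: the programme, with n = 30, "will be performed in three groups of 10 participants", and the control group is also given as n = 30. Study design likewise gives 30 versus 30.

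Two BMI classes are eligible. Table 1 asks for: "Overweight or grade I obese pregnant woman aged 25–40 years old with a normal pregnancy course". The expected mix of the two classes is not given.

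Statistical analysis adjusts each outcome for its baseline value. A second model adds age and any other confounder that turns out poorly balanced, and both results are reported.

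**The concern.** The stated allocation method and the stated design do not fit together. An unrestricted list fixes the probability for each woman but not the total in each arm, so an exercise arm of exactly 30 in three equal classes is an outcome that happens only sometimes.

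The same list leaves the split of overweight and grade I obese women to chance. BMI class is known before randomisation, so it could be balanced at little cost. Its link with weight gain and glycaemia is a plausible assumption: the Background ties overweight and obesity to gestational diabetes but gives no figure for these outcomes. In a trial of 60, a sizeable gap in BMI mix would make the primary comparisons harder to read. The planned response is a covariate chosen after the imbalance has been seen.

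**Working it through.** **Inputs.** From Sample size: difference 1.04 kg, SD 1.15 kg, power 90%, α 0.05, 26 per group evaluable, 15% loss, 60 recruited. From Randomization and blinding: simple, 1:1. From Exercise intervention: 3 × 10 = 30. Assumed: a two-sided test, and a share of grade I obese women between 30 and 50%.

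**1. The plan's own sample size.** n per group = 2 × [(z₀.₉₇₅ + z₀.₉₀) × SD / Δ]² = 2 × [(1.960 + 1.282) × 1.15 / 1.04]² = 25.7, so 26 per group. This reproduces "A total of 52 women (26 per group) will be needed". The t-test version gives 26.7, so 27. For loss, 52 × 1.15 = 59.8, so 60, matches the plan; 52 / 0.85 = 61.2, so 62, is two women more. The sample size is not at fault on this point.

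**2. Arm sizes under simple randomisation.** The number in the exercise arm is X ~ Binomial(60, 0.5).

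- P(X = 30) = C(60, 30) / 2⁶⁰ = 0.103
- P(X > 30) = (1 − 0.1026) / 2 = 0.449
- P(33:27 or more uneven) = 0.519
- P(35:25 or more uneven) = 0.245
- P(40:20 or more uneven) = 0.013

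**3. Effect on power.** Two-sample t-test, standardised difference 1.04 / 1.15 = 0.904.

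| Analysed | Split | Power |
|---|---|---|
| 60 | 30:30 | 93.1% |
| 60 | 25:35 | 92.4% |
| 60 | 20:40 | 90.1% |
| 60 | average over simple randomisation | 92.7% |
| 52 | 26:26 | 89.2% |
| 52 | average over simple randomisation | 88.6% |

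The average loss is 0.4 points with 60 analysed and 0.6 points with 52.

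**4. BMI class.** Simulation, 400,000 draws per row. The gap is the absolute difference between arms in the share of obese women.

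| Assumed share obese | P(gap ≥ 10 points), simple | P(gap ≥ 20 points), simple | P(gap ≥ 20 points), 30:30 forced without strata |
|---|---|---|---|
| 30% | 0.42 | 0.10 | 0.16 |
| 40% | 0.43 | 0.13 | 0.19 |
| 50% | 0.52 | 0.16 | 0.20 |

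Forcing 30:30 alone therefore does not help BMI balance. The slightly higher figures in the last column arise partly because, with 30 per arm, the gap moves in steps of 2/30 and can land exactly on 20 points.

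**5. What stratified blocks would give.** With blocks of 4 and 6 chosen at random within two BMI strata, and 30 to 50% obese, simulated trials end at exactly 30:30 about 55% of the time and have more than 30 in the exercise arm about 23% of the time. The limits follow directly. An unfinished block of 6 can leave a stratum at most 3 women apart, so two strata give at most 6 apart, which is 33:27. If the strata err in opposite directions, the arms are 30:30 and the gap in share obese is 3/30 = 10 points. With blocks of 4 only, each stratum is at most 2 apart, and the worst total is 32:28.

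**The case against.** The best case for the plan is that simple randomisation is valid, unbiased and the least predictable scheme, which matters when participants know their group. The figures of 30 per group and three classes of 10 can be read as planning targets under a 1:1 ratio. Baseline adjustment and the second model absorb part of any BMI imbalance, and both models are reported. An article may also use *simple* loosely for a balanced list.

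Much of this stands, and it rules out several stronger readings:

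- **That the method biases the comparison or costs material power.** It does neither: the average loss is under 1 point.
- **That an arm of 25 or fewer (24.5% of trials) falls below the required 26 and so fails.** The 26 comes from an equal-allocation calculation, and power depends on both arms. A 25:35 split of 60 still has 92.4%.
- **That 44.9% is the chance of exceeding class capacity.** Nothing in the article makes 10 a maximum, nor says that classes are filled from consecutive allocations. The figure is only the chance of more than 30 in the exercise arm.
- **That BMI will be unbalanced.** It is uncontrolled. Balance holds in expectation, and large gaps are a minority outcome.

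What the objection does not remove is that a named method and exact sizes are both stated and do not agree. This is not a detail left to another document. Nor does adjustment for baseline values reach every primary outcome: the cord-blood glucose/insulin ratio has no baseline value to adjust for.

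**Conclusion.** The point holds as an inconsistency and a missed, inexpensive safeguard. Under the stated method about nine trials in ten (89.7%) would not have 30 per group. The chance of a 20-point gap in share obese is about 10 to 16%. The arm-size figures are exact, given 60 women and independent 1:1 allocation. The BMI figures rest on the assumed 30 to 50% obese, and the importance of such a gap rests on BMI being prognostic, which the article does not quantify. The harm lies in balance and in delivering the design as described. The validity of the randomisation and the sample size are not in question.

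**What to change.** Replace the simple sequence with computer-generated permuted blocks of concealed, randomly varying size (for example 4 and 6), stratified by overweight versus grade I obese and prepared by the same independent team member. Prespecify baseline BMI as a covariate in the primary model, so that it does not depend on the rule for confounders found poorly balanced. State 30 per group and 10 per class as targets.

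If the intention was a list constrained to 30 + 30, correct the word *simple* in Randomization and blinding and describe the restriction. That settles the arm sizes, but BMI class would still need strata or the prespecified covariate. Closing an arm informally once it reaches 30 is no substitute, because every later allocation would then be known.

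Before enrolment the cost is one new list and a few sentences; BMI is already collected. Two downsides should be stated: slightly more predictability in a trial where participants know their group, limited by the concealed varying block sizes; and arm sizes that stay close to 30:30 but are not guaranteed (exact in about 55% of simulated trials, at worst about 33:27).

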## Exercise intervention

Most of exercise programs developed for pregnant women until now [20, 27, 52] have been designed in compliance with the recommendations of the American College of Obstetrics and Gynaecology (ACOG) in 2002 [53], or the Canadian Society for Exercise Physiology, among others [54]. However, in 2011, Zavorsky & Longo [55] launched a more actual, specific, and evidence-based guideline for exercise programs during pregnancy. Consequently, the exercise program that will be conducted in the present project has been developed accordingly to this guideline [55]. Nonetheless, we have also followed similar studies [56, 57] where aerobic and resistance training, as well as strengthening of the pelvic floor muscles [58], have been developed successfully and in line with these recommendations [57].

The exercise intervention (*n* = 30) will be performed in three groups of 10 participants and will meet the training standards of the American College of Sports Medicine [59] for adults. The groups will train 3 days/week (55–60 minutes per session) from the 17th week of gestation until delivery. The exercise sessions will be designed, carefully supervised, guided and instructed by qualified exercise professionals with experience in working with pregnant women.

The exercise program planning is shown in Table 3. The exercise intervention group will have different phases: a) *Information phase*: which will involve the understanding of the intervention plan for them, the goals we want to work with them, and how we will perform it (one training session); b) *Movement Learning phase*: theoretical and practical sessions with the explanation of movements and explanation of basic movement patterns (two training sessions); and c) *Physical Fitness Training phase*: with training sessions aimed at improving fitness and weight management (from the 18th until the 34th gestational week), and training sessions focused on a correct pelvic mobilization for the delivery (after the 34th gestational week until delivery) in order to try to reduce caesarean section rate, delivery time and number of pushes [23, 60].

**Table 3 Tab3:** Supervised exercise intervention program

SESION STRUCTURE	CONTENT										
WARM-UP 10 min	Joint mobility and different walk modalities										
CONDITIONING 40 min	Training week	1	2–4	5–6	7–8	9–10	11–12	13–14	15–16	17–18	>19
	Gestational week	17	18–20	21–22	23–24	25–26	27–28	29–30	31–32	33–34	>34
	Intensity (RPE)		12–13	12–13	13–14	13–14	14–15	14–15	15–16	15–16	
	Monday CIRCUIT (muscular and cardiovascular blocks)	Familiarization and acquisition of the basic movement patterns	5 RE × 3	5 RE × 3	5 RE × 3	5 RE × 3	5 RE × 3	5 RE × 3	5 RE × 3	5 RE × 3	Pelvic movements + integration pattern. Real transfer to delivery moment
			1 min REST	1 min REST	1 min REST	1 min REST	1 min REST	1 min REST	1 min REST	1 min REST	
			1 AE 5′	1 AE 5′	1 AE 5′	1 AE 5′	1 AE 5′	1 AE 5′	1 AE 5′	1 AE 5′	
			1 min REST	1 min REST	1 min REST	1 min REST	1 min REST	1 min REST	1 min REST	1 min REST	
			5RE ×3	5RE ×3	5RE ×3	5RE ×3	5RE ×3	5RE ×3	5RE ×3	5RE ×3	
			1AE 5′	1AE 5′	1AE 5′	1AE 5′	1AE 5′	1AE 5′	1AE 5′	1AE 5′	
			1 min REST	1 min REST	1 min REST	1 min REST	1 min REST	1 min REST	1 min REST	1 min REST	
	Wednesday (cardiovascular block)	Familiarization and acquisition of the basic movement patterns	Choreographies and aerobic exercises								Pelvic movements + integration pattern. Real transfer to delivery moment
	Friday CIRCUIT (muscular and cardiovascular blocks)	Familiarization and acquisition of the basic movement patterns	5 RE × 3	5 RE × 3	5 RE × 3	5 RE × 3	5 RE × 3	5 RE × 3	5 RE × 3	5 RE × 3	Pelvic movements + integration pattern. Real transfer to delivery moment
			1 min REST	1 min REST	1 min REST	1 min REST	1 min REST	1 min REST	1 min REST	1 min REST	
			1 AE 5′	1 AE 5′	1 AE 5′	1 AE 5′	1 AE 5′	1 AE 5′	1 AE 5′	1 AE 5′	
			1 min REST	1 min REST	1 min REST	1 min REST	1 min REST	1 min REST	1 min REST	1 min REST	
			5RE ×3	5RE ×3	5RE ×3	5RE ×3	5RE ×3	5RE ×3	5RE ×3	5RE ×3	
			1AE 5′	1AE 5′	1AE 5′	1AE 5′	1AE 5′	1AE 5′	1AE 5′	1AE 5′	
			1 min REST	1 min REST	1 min REST	1 min REST	1 min REST	1 min REST	1 min REST	1 min REST	
COOL-DOWN 10 min	Myofascial release, stretching and relaxation exercises										

*RPE* rating of perceived exertion, *RE* resistance exercise, *AE* aerobic exercise, *REST* resting. The load will be gradually and individualized increased for each participant to reach the intensity designed for each session

The exercise intensity will be prescribed as percentages of heart rate reserve (% HRR) [55] and the ratings of perceived exertion (RPE) using the Borg 6–20 RPE scale [61]. We will also employ the Karvonen formula to estimate the training heart rate (e.g. 65 % HRR for a pregnant with 185 bpm maximum heart rate and 80 bpm basal heart rate would be calculated as: Training Heart Rate = 0.65 * (185–80) + 80). Heart rate will be measured with heart rate monitors (Polar Electro OY, Finland) to control the intensity of the sessions. One third of the participants in the intervention group will wear heart rate monitors in 1/3 of the sessions, both randomly selected. Intensity (expressed as RPE) will be expected to range from 12 to 16.

The intensity will be adapted during the exercise program based on the week of gestation and each woman’s heart rate. The *Physical Fitness Training phase* sessions until the 34th gestational week will consist of mixed work, composed of circuits where both muscular and cardiovascular conditioning will be implemented. This type of exercise training has been already developed by White et al. [57] who demonstrated better results for both the prevention of GDM, preeclampsia and preterm births, and for increased vaginal vs. caesarean deliveries.

Each training session will include 10 min warm-up with walks, mobility and activation exercises. The main part will consist of 40 min exercises organized in circuit. The circuit will alternate muscular and cardiovascular blocks of concurrent training. Each muscle circuit will consist of a hip dominant movement exercise (e.g. deadlift exercises, hinge hip, swing hip), a dominant knee (e.g. squats, lunges) 2 pull movements, 1 push movement (push-ups adapted) and 1 CORE muscles movement. Cardiovascular blocks will take approximately 3 min and will be composed of aerobic exercises as different variants of step-ups, small choreographies, front and side trips. Sessions will finish with a 10 min cool-down period of stretching, breathing, relaxation exercises and myofascial relief [62]. None of the proposed exercises will include Valsalva manoeuvre, supine positions, or high impact exercises that could go in detriment of the successful activation of the lumbo-abdominal belt, promote a decrease in venous return or alterations in blood pressure, among others. The exercise program volume and intensity programmed is also shown in Table 3.

To maximize adherence, several strategies will be implemented including music in all sessions and telephone calls following missed sessions. The researchers will control and register the presence of adverse events during the class and between classes.

The participants randomly assigned to the control group (*n* = 30) will receive general advices about the positive effects of PA during pregnancy for her and the foetus’s health status. The researchers will give three seminar explaining 1) the benefits of exercise for a better pregnancy, prevention and treatment of GDM and excessive weight gain; 2) ergonomic advises, exercises to perform at home (e.g. stretching, resistance training) and strategies to increase their daily PA levels; 3) the benefits of the Mediterranean Diet and nutritional education. Moreover, we will prepare brochures describing the overall benefits of PA on health, and we will dispense general guidelines to increase the level of daily PA and optimum nutrition during pregnancy [63, 64].

